## Duration of Therapy

*MBSR arm*: Total duration of the MBSR curriculum is 8 weeks with a once weekly session (over Zoom or in person) for 2 hours and a full day mindfulness retreat.

*MBSR + PAP arm*: Total duration is the same as above for the MBSR curriculum with a 9 week total duration (given additional integration session following MBSR completion). This arm will include an additional time to incorporate the PAP protocol. This includes three 90min preparatory sessions, one 8 hour psilocybin session (in place of the MBSR retreat), and three 90 minute integration sessions.

### Criteria for discontinuation of study treatment

Patients may withdraw from treatment or the study overall at any time at their own request, or they may be withdrawn at the discretion of the Investigator for safety, behavioral reasons, or the inability of the subject to comply with the protocol-required schedule of study visits or procedures. The following will result in treatment discontinuation:

- Subject requests to discontinue the study treatment and/or study procedures.
- Non-compliance as defined as missing any of the MBSR or PAP sessions.
- Pregnancy
- Significant protocol violation
- The subject refused further treatment
- Study terminated by investigator sponsor
- Lost to follow-up
- Concerns about resultant abuse of study drug or related compounds

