# STUDY DESIGN

## Description

Recruitment will target physicians or nurses with at least 1 month of frontline clinical experience during the COVID pandemic who meet DSM-5 criteria for a depressive disorder, including adjustment disorder with depressed mood.

Participants that meet eligibility criteria and have a screening MBI-HSS (MP) score that meets our working definition of burnout (emotional exhaustion subscale ≥ 27) and a ‘high’ score on one other subscale (either depersonalization ≥ 13 or personal accomplishment ≤ 21) as well as a PHQ-9 depression screen ≥ 10 will be offered enrollment and following a consenting process will be randomized to either MBSR or MBSR + PAP with 12 participants per group. PHQ-9 and MBI-HSS questionnaires may be administered prior to consenting to assess eligibility. Consenting will be completed in person with paper or electronic consenting forms. The MBSR group will complete an 8-week MBSR curriculum (online) through the University of Utah Resiliency Center led by [name], LCSW which includes a weekly 2.5-hour sessions over Zoom for 8 weeks and an 8 hour in-person retreat between weeks 6 and 7. If capacity within the University of Utah MBSR groups limits enrollment and feasibility we will incorporate the MBSR programs through Intermountain as well as Davis Behavioral Health. We will run subjects through the MBSR curriculum in flexible numbers concurrently until a total of 12 have completed this arm. The MBSR + PAP group will complete this same curriculum, however will substitute an 8-hour group-format psilocybin-assisted therapy session (with 25 mg psilocybin capsule) with 1:1 therapist to participant ratio instead of the MBSR retreat day. Each participant will have an assigned individual therapist present for the duration of the psilocybin dosing session. A lead therapist ([name] PhD) will also be present for all study sessions including the psilocybin dosing day and there will be at least one lead study monitor present for the duration of the psilocybin dosing day ([name] MD or [name] MD). The psilocybin intervention will be completed in groups of 2-6 individuals per cohort. Additionally, the MBSR + PAP group will have 3, 90-minute group preparatory sessions prior to the psilocybin session and 3 subsequent 90-minute integration sessions. The first integration session will occur 1-2 days following the psilocybin session. A communal music track will be played during the PAP session. After the enrollment and treatment of the first four patients, accrual will be placed on hold to ensure participant safety. If stopping rules are not met, we will continue with enrollment.

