
PAP Preparation sessions will focus on psychoeducation regarding the effects of psilocybin, guidance as to navigating the experience, establishing safety and trust with the therapist team, and specific mindfulness focused skills (drawing on the MBSR curriculum) that can be employed during the experience. The psilocybin session will employ a 1:1 therapist to participant ratio which is the same model as the HOPE trial run by this team. These sessions will also be video recorded with participant consent. This session will be conducted in a largely non-directive and supportive fashion similar to the current therapy model used in psychedelic-assisted therapy research. However, we will book-end the dosing day with specific mindfulness exercises drawing from the MBSR curriculum. At the end of this 8-hour session all participants will be assessed for safety to leave the premises including a screen for suicidality, a final set of vital signs and medical evaluation, as well as a cognitive assessment as to orientation. Rides and support person will be confirmed by the study team. The first integration session will occur within 48 hours of this dosing day however the therapist team will be available by phone throughout this time in case there is need for additional support. Subsequent integration sessions (2 additional) will be integrated into the MBSR curriculum, following the weekly group MBSR session. These sessions will focus on processing the experience and relevant emotional and psychological material as a group as well as integrating this with perspectives and insights gained through the mindfulness curriculum.

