**Table 2: Schedule of Events**

| **Week** | **-5 to -1** | | **1** | **2** | **3** | **4** | **5** | **6** | **7** | **8** | **9** | **11** | **33** |
| --- | --- | --- | --- | --- | --- | --- | --- | --- | --- | --- | --- | --- | --- |
| **Day** | **-35 to -7** | | **0-7** | **8-14** | **15-21** | **Etc.** |  |  |  |  |  |  |  |
| **Study Stage** | **Screen** | | **Active** | | | | | | | | | **Follow-up^[[1]](#endnote-1)^** | |
| Informed consent, registration | x |  |  |  |  |  |  |  |  |  |  |  |  |
| Eligibility criteria | x |  |  |  |  |  |  |  |  |  |  |  |  |
| Demographics | x |  |  |  |  |  |  |  |  |  |  |  |  |
| Medical History | x |  |  |  |  |  |  |  |  |  |  |  |  |
| Vitals and PE^[[2]](#endnote-2)^ | x |  |  |  |  |  |  |  |  |  |  |  |  |
| Randomization/assignment | **x** |  |  |  |  |  |  |  |  |  |  |  |  |
| Expectancy Questionnaires |  | **x** | **x** |  |  |  |  |  |  |  |  |  |  |
| **MBSR ARM** |  |  | **1** | **2** | **3** | **4** | **5** | **6** | **7** | **8** | **9** | **11** | **33** |
| **MBSR course** |  |  | **x** | **x** | **x** | **x** | **x** | **x** | **x** | **x** |  |  |  |
| **Retreat** |  |  |  |  |  |  |  |  | **x** |  |  |  |  |
|  |  |  |  |  |  |  |  |  |  |  |  |  |  |
| **PAP-MBSR** |  |  | **1** | **2** | **3** | **4** | **5** | **6** | **7** | **8** | **9** | **11** | **33** |
| Comprehensive Metabolic Panel ^xi.^ |  | x |  |  |  |  |  |  |  |  |  |  |  |
| Urine drug screen |  | **x** |  |  |  |  |  | x (within 24 hrs) |  |  |  |  |  |
| Pregnancy test ^iii^ |  | x |  |  |  |  |  | x (within 8 days of PAP) |  |  |  |  |  |
| MBSR Course |  |  | **x** | **x** | **x** | **x** | **x** | x | x | **x** |  |  |  |
| Prep Sessions 1-3 |  |  |  |  |  |  | **x** | x |  |  |  |  |  |
| PAP Session |  |  |  |  |  |  |  |  | x |  |  |  |  |
| Vitals monitoring |  |  |  |  |  |  |  |  | **x^[[3]](#endnote-3)^** |  |  |  |  |
| Integration Sessions 1-3 |  |  |  |  |  |  |  |  | **x** | **x** | **x** |  |  |
| **Assessments** |  |  | **1^[[4]](#endnote-4)^** | **2** | **3** | **4** | **5** | **6** | **7** | **8^[[5]](#endnote-5)^** | **9** | **11** | **33** |
| PHQ-9 | x |  |  |  |  |  |  |  |  |  |  |  |  |
| MBI-HSS (MP) | x |  | x |  |  |  |  |  |  |  |  | x | **x** |
| QIDS-SR-16 |  |  | x |  |  |  |  |  |  |  |  | x | **x** |
| Demoralization II scale |  |  | x |  |  |  |  |  |  |  |  | x |  |
| PTSD Checklist 5 |  |  | x |  |  |  |  |  |  |  |  | x | **x** |
| MEQ-30 |  |  |  |  |  |  |  |  | x |  |  |  |  |

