#### Pre-Psilocybin Session #2:

Topics will include a review of psilocybin treatment setting, rules of conduct during psilocybin session including how to handle occasional bathroom/stretching breaks, review of safety guidelines including the rule about no leaving the treatment area, how to handle fear and other challenging emotions, review of rules around physical touch between therapist and participant, review of the use of eyeshades and headphones, and instructions about music.

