# STATISTICAL CONSIDERATIONS

## Population for analyses

12.1.1 Safety Data Set. All participants enrolled in the trial will be eligible for the safety data set. AEs and suicidality per C-SSRS will be assessed across both study arms.

12.1.2. Evaluable for intent-to-treat (ITT) analysis. All participants enrolled in the trial and randomized to either MBSR + PAP or MBSR only will be eligible for the (ITT) analysis. The primary analysis will involve intention to treat analyses on all study outcomes.

12.1.2 Evaluable for per-protocol analysis. Participants in the MBSR arm who have completed two-thirds of the MBSR sessions will be considered evaluable for the per-protocol efficacy data set. Participants in the MBSR + PAP arm who have completed two- thirds of the MBSR sessions (excepting the MBSR retreat) *as well as* two out of three of the preparatory sessions, the psilocybin therapy session, two out of the three integration sessions, and a baseline and post-psilocybin QIDS-SR and MBI will be considered evaluable for the per-protocol efficacy data set.

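### Section 6.4 ends treatment after any one missed session, so a PAP participant can lose the single psilocybin dose at an attendance level that section 12.1 accepts as per-protocol

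*Protocol*

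**What the plan says.** - **Discontinuation rule.** Section 6.4 (Criteria for discontinuation of study treatment) states a list of events that will end treatment. One entry is "Non-compliance as defined as missing any of the MBSR or PAP sessions". The separate off-study list in the same section does not mention missed sessions.
- **Per-protocol set.** Section 12.1 asks PAP-arm participants for two-thirds of the MBSR sessions (not counting the retreat), then "two out of three of the preparatory sessions, the psilocybin therapy session, two out of the three integration sessions", plus baseline and post-psilocybin QIDS-SR and MBI.
- **Primary analysis set.** Section 12.1 makes intention to treat primary: "All participants enrolled in the trial and randomized to either MBSR + PAP or MBSR only will be eligible for the (ITT) analysis".
- **Timing of the dose.** Section 4.1 places "an 8 hour in-person retreat between weeks 6 and 7" in the MBSR curriculum, and the psilocybin session replaces it in the PAP arm. Table 2 shows the session in week 7, and section 6.1 lets it move by one week either way.
- **Flexibility offered.** Sections 6.1 and 9.4 allow Zoom attendance at one preparatory and up to two integration sessions, the one-week shift of the dose, and flexible scheduling of preparatory sessions. Nothing lets a missed MBSR class be made up.
- **Meaning of PAP sessions.** Section 4.1 uses the label for preparation: "PAP Preparation sessions will focus on psychoeducation regarding the effects of psilocybin". Section 6.4 says "This arm will include an additional time to incorporate the PAP protocol" and then lists preparatory, dosing and integration sessions together. Table 2, however, gives "Prep Sessions 1-3" and the integration sessions rows of their own, apart from the PAP session.

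**The concern.** The rule that decides who continues treatment is much stricter than the rule that decides who counts as adequately treated. In the PAP arm that matters more than usual, because the drug is given once and late. A participant stopped for one missed class in the first six weeks has attended nearly everything held so far, but does not reach the dose that defines the arm.

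That participant is still analysed in the PAP arm. Each such case makes the two arms more alike and pulls the QIDS-SR-16 difference towards zero. It also shrinks the per-protocol set below what section 12.1 was written to admit.

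If PAP sessions include preparation and integration, the mismatch widens. One missed preparatory session would bar dosing. Missing integration session 1 or 2 would end treatment before two of three could be attended.

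**Working it through.** **Plan's own figure.** The Statistical Power section gives about 81% power for 12 per arm, d = 1.0, ICC 0.5 and alpha 0.05. A baseline-adjusted normal approximation matches it: SE = √[(1 − 0.5²) × 2/12] = 0.354; 1.0/0.354 = 2.83; Φ(2.83 − 1.96) = 80.7%. The protocol does not say which model was simulated. A plain change-score version gives 68.8%, so this is only a reference point for the last step.

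**Two thresholds for the same person.** One missed class leaves 7/8 = 87.5%, or 8/9 = 88.9% if there are nine classes. (Sections 4.1 and 6.4 and Table 2 give eight; sections 6.1 and 9.3 say nine.) Two-thirds requires 6 of 8 or 6 of 9. Either way the person is discontinued under 6.4 while meeting the MBSR part of 12.1.

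**Share still eligible for dosing.** Attendance q per class is an assumption, because the protocol gives none. With n classes before dosing and independent attendance, the share is qⁿ. The one-week window gives n = 5 to 7. The clustered column is E[qⁿ] with q drawn from a Beta distribution with intra-person correlation 0.3, also assumed.

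| q | n = 5 | n = 6 | n = 7 | Eligible of 12 (n = 6) | n = 6, clustered |
|---|---|---|---|---|---|
| 0.95 | 0.774 | 0.735 | 0.698 | 8.8 | 0.843 |
| 0.97 | 0.859 | 0.833 | 0.808 | 10.0 | 0.903 |
| 0.98 | 0.904 | 0.886 | 0.868 | 10.6 | 0.935 |
| 0.99 | 0.951 | 0.941 | 0.932 | 11.3 | 0.967 |

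**Broad reading of PAP sessions.** Adding three preparatory sessions gives q⁹ = 0.630, 0.760, 0.834 and 0.914 (clustered 0.811, 0.883, 0.920 and 0.960).

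**With the rule tied to two-thirds.** Taking eight classes, the threshold is still reachable at dosing if at least 4 of the first 6 are attended. P(Bin(6, q) ≥ 4) = 0.9978 at q = 0.95 and 0.9998 at 0.98 (clustered 0.961 to 0.993 over 0.95 to 0.99). Nine classes would be more lenient.

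**Dilution, as illustration only.** Suppose participants stopped before the dose do equally well in both arms, and everyone else differs by d = 1.0. Then the intention-to-treat d equals the share dosed. For six classes:
- q = 0.95: d = 0.735; Φ(0.735 × 2.83 − 1.96) ≈ 55% power (clustered about 66%).
- q = 0.98: d = 0.886; power about 71% (clustered about 75%).

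**The case against.** **A conduct rule may be stricter than an analysis set.** This stands. Section 6.4 governs treatment and section 12.1 governs evaluability. Section 12.1 also keeps a role under strict enforcement: someone who misses only the last integration session can be discontinued and still be per-protocol. A reader might infer that the two sections contradict each other outright; they do not. They are misaligned, and the misalignment bites before dosing.

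**Not dosing is not certain.** The opening of the 6.4 criteria leaves some withdrawals to the investigator, including for inability to keep to the visit schedule. Section 7 asks for every effort to give psilocybin as planned. Section 6.1 lists what must hold to receive psilocybin and names no attendance condition. These make practice harder to predict, but none overrides a bullet under a mandatory heading. If staff ignore the bullet, each case departs from the protocol, and who is dosed rests on unwritten judgement in an open-label trial.

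**The sizes are assumed.** This is correct. Zoom classes and flexible scheduling may keep absences low. The misalignment itself does not depend on the rates.

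**This is a pilot.** Power matters less when the stated goal is estimation and feasibility. But an effect estimate diluted by an attendance rule is also a poor basis for planning the next trial.

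**Conclusion.** The point holds as a misalignment worth fixing. As written, section 6.4 withholds the single dose after one missed MBSR class, although section 12.1 would accept that attendance. The affected participants stay in the PAP arm for the primary analysis. Whether one missed preparatory or integration session has the same force depends on a term that 6.4 does not define.

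The size is unknown. Over six classes with independent attendance of 95% to 99%, 74% to 94% would remain eligible for dosing; clustered absences give 84% to 97%. The shrinkage of d rests on the further assumptions stated with it and should not be read as a forecast.

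Three stronger inferences are not supported:
- **That a dosed participant with one miss is automatically per-protocol.** Section 12.1 also requires the preparatory and integration minimums and the baseline and post-psilocybin QIDS-SR and MBI.
- **That the 16 of 24 retention criterion or intention-to-treat membership is threatened.** Missed sessions are not a reason to leave the study. The effect on the count of participants completing each modality (section 1.1) is open, because completion is not defined there.
- **That an exact loss can be stated for the MBSR arm.** The session count is inconsistent across sections, so the number that makes up two-thirds is not settled.

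**What to change.** Replace the any-missed-session bullet in section 6.4 with these rules:

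1. **MBSR classes.** Discontinue only when two-thirds of the scheduled sessions, as in section 12.1, can no longer be met. State this as a fraction, or settle first whether there are eight or nine classes.
2. **Integration sessions.** Discontinue only when two of three can no longer be met.
3. **Preparatory sessions.** Set an explicit minimum before dosing as a safety decision, and make section 12.1 match. Session 2 includes "review of safety guidelines including the rule about no leaving the treatment area", and session 3 covers emergency procedures and the private room. A requirement for all three, with a make-up session allowed, would therefore be defensible; so would two of three if the team judges that safe.
4. **Definition.** Say in section 6.4 which sessions the term PAP sessions covers.

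The cost is amendment wording in section 6.4, and in section 12.1 if the preparatory minimum is not two of three. No new data are needed, and a make-up session arises only if that option is chosen. The downside is that some participants will be dosed after a missed class, which section 12.1 already accepts for the per-protocol set.

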### Criteria for discontinuation of study (“off study”)

Subjects will be taken off study for the following:

- The subject completed the study follow-up period
- Screen failure
- Subject is lost to follow-up
- If, in the investigator's opinion, the continuation of the trial would be harmful to the subject's well-being.
- Concerns about resultant abuse of study drug or related compounds
- Development of intercurrent illness or situation which would, in the judgment of the investigator, significantly affect assessments of clinical status and trial endpoints.
- Participant requests to be withdrawn from the study
- Death

# TOXICITIES AND DOSE MODIFICATION

Every effort should be made to administer psilocybin at the planned dose and schedule. In the event of study drug-related adverse event, supportive care and therapy will be administered. Patients are to be instructed to notify investigators at the first occurrence of any adverse symptom. Appropriate follow-up assessments should be done until adequate recovery occurs as assessed by the Investigator.

## Guidelines for the Management of Adverse Events

Since the resurgence of interest in psilocybin as a therapeutic tool in the early 1990s, there have been no reports of any medical or psychiatric serious adverse events. This includes over 2000 doses of psilocybin (in various amounts) that have been safely administered to humans in the United States and Europe, in carefully controlled scientific settings. However, to assure the safety of our participants, protocols will be in place should any adverse events occur.

Emotional difficulties, often termed “difficult experiences” are not necessarily pathological in themselves and can be understood as part of the therapeutic process (e.g., working through cancer-related psychological or existential distress). These displays may include shouting, tearfulness, and other emotive displays that the therapist will attempt to work through with the subject. However, in the case of extreme emotional distress (as defined by the subject) or counter-therapeutic experiences, subject physical and psychological safety will continue to be assured in a systematic manner. Subjects will be offered the following in a stepwise fashion:

1. The group leader will provide additional supportive intervention in cooperation with the subject’s assigned therapist such that the subject’s concerns are addressed to the best of their ability, while maintaining the group setting.
2. If support from the group leader cannot address the individual’s concern after 30 minutes, or if the amount of distress is judged by the group leader to be counter-therapeutic or significant enough to require more individual attention, the subject will then be relocated to an attached private room with their individual therapist where they will be provided with supportive therapy and suggestions for mindfulness strategies. The environment will be crafted as such that the subject is both safe and comfortable.
3. If interventions in the individual room do not alleviate the subject’s concerns after 60 minutes, they will be offered orally administered lorazepam 2mg.
4. At the end of the psilocybin dosing day if there are clinical concerns that a given participant is not safe to leave the site along medical, psychiatric, or cognitive assessments the lead study monitor (one of the PIs) and the Lead Therapist will remain on site for ongoing assessment and support until the participant is deemed safe to depart with a designated ride and support person. If a given participant remains unsafe to leave the site despite ongoing assessment and support they will be escorted to either the HMHI Receiving Center (for psychiatric assessment and care) or the University of Utah Emergency Department depending on either psychiatric or medical clinical presentation. Presenting features that would preclude participants from leaving the study site following the psilocybin dosing day include: acute medical conditions or significant side effects to psilocybin that are not improving and represent clinically concerning risk per MD assessment, acute suicidality or thoughts of self harm or severe emotional distress that is judged to represent clinically significant impairment in functioning or safety concerns based on MD assessment, or cognitive impairments deemed to present clinically significant impairments in functioning based on MD assessment.

Of note, there have been no reports of the necessity of pharmacologic interventions for psychological safety in any well-reported clinical trials with oral psilocybin. However, to assure the safety of the subjects, these materials and protocols will be readily available and in place.

Although are no recorded incidents in controlled studies with similar or higher doses that were deemed serious, protocols will be in place for physical adverse events as well. Most commonly, these include transient mild increases in systolic and/or diastolic blood pressure, mild headache, mild tachycardia, and nausea after psilocybin administration. Hydralazine (25mg), acetaminophen (650mg), propranolol (10mg), and promethazine (25mg) will be available to address these concerns if deemed necessary by a licensed physician in the study after a clinical examination of the study subject. Vital signs will be monitored approximately ten minutes before and 30, 60, 90, 120, 180, 240, 300, and 360 minutes after administration consistent with previous studies. This will include heart rate, respiratory rate, blood pressure, and oxygen saturation. If there is a medical emergency, participants will be escorted by an on-call clinician to the University of Utah Emergency Department by EMS. If there is a psychiatric emergency the participant will escorted by an on-call physician to the HMHI Receiving Center for evaluation.

